## Abstract

**Background:**

Carotid artery stenting (CAS) is an effective revascularization procedure for internal carotid artery stenosis, but it is associated with a high incidence of perioperative cerebral embolism, with asymptomatic and symptomatic embolic events occurring in up to 40% of patients. Transcranial Doppler (TCD) has been shown to enhance fibrinolysis through sonothrombolysis and may reduce embolic burden during carotid interventions.

**Aims:**

To evaluate whether intraoperative and post-procedural TCD monitoring can reduce the number of new diffusion-weighted imaging (DWI) lesions after CAS in patients with severe internal carotid artery stenosis.

**Sample size estimates:**

A total of 232 patients are required to detect a 50% reduction in the median number of new DWI lesions (from 2.0 to 1.0) with 80% power and a two-sided *α* of 0.05, accounting for a 5% dropout rate.

**Design:**

TCD-ICAS is a prospective, randomized, single-center, blinded endpoint trial. Patients scheduled for CAS are randomized 1:1 to receive either TCD treatment (1.6 MHz, 0.274 MPa) from femoral artery puncture until 30–60 min after procedure completion plus standard care, or standard care alone.

**Outcomes:**

The primary efficacy endpoint is the number of new DWI lesions at 24 h post-randomization. The primary safety endpoint is intracranial hemorrhage within 24 h.

**Conclusion:**

The TCD-ICAS trial will assess the efficacy and safety of TCD as an adjuvant therapy to reduce cerebral embolic events in patients undergoing CAS.

**Clinical trial registration:**

Identifier (NCT07462546).

## Introduction

Carotid artery stenting (CAS) is a widely performed procedure for stroke prevention in patients with severe internal carotid artery stenosis (1–3). However, perioperative cerebral embolism remains a significant concern, with studies reporting new ischemic lesions on DWI in a substantial proportion of patients post-CAS (4).

Transcranial Doppler ultrasound is a non-invasive, real-time monitoring tool capable of detecting microembolic signals during carotid interventions (5). Beyond its diagnostic utility, emerging evidence suggests that TCD may exert therapeutic effects through ultrasound-enhanced thrombolysis (sonothrombolysis) (6–11). The SONOBUSTER trial demonstrated that TCD monitoring during carotid endarterectomy and stenting significantly reduced the incidence of new brain infarctions (12). Similarly, the SONOBIRDIE trial showed a reduction in cerebral embolism and stroke recurrence with TCD use during carotid endarterectomy (13). The proposed mechanism involves acoustic cavitation, which mechanically disrupts thrombus structure and enhances fibrinolytic drug penetration (14).

Building on these findings, we hypothesize that TCD application during and after CAS may reduce the number and volume of perioperative cerebral emboli, thereby decreasing the incidence of new ischemic lesions and improving clinical outcomes. The TCD-ICAS trial is designed to test this hypothesis in a randomized, controlled setting.

## Methods

### Study design

The TCD-ICAS trial is a prospective, randomized, single-center, blinded endpoint trial conducted at the General Hospital of Northern Theater Command, Shenyang, China. This study followed the Consolidated Standards of Reporting Trials (CONSORT) reporting guidelines. The trial flowchart is shown in Figure 1.

**Figure 1 fig1:**
[figure not shown]
Study flowchart. CAS, carotid artery stenosis; TCD, Transcranial Doppler; NIHSS, National Institutes of Health Stroke Scale; MRI, magnetic resonance imaging; mRS, Modified Rankin Scale.

### Study population

In TCD-ICAS trial, eligible patients are adults with severe internal carotid artery stenosis scheduled for CAS who have adequate temporal bone window for TCD insonation. Key exclusion criteria include severe systemic infection or major organ dysfunction; intracranial hemorrhage within 90 days; severe coagulation disorders. Patients will be enrolled at General Hospital of Northern Theater Command between March 2026 to September 2027. The detailed inclusion and exclusion criteria are shown in Table 1.

**Table 1 tab1:** The inclusion/exclusion criteria.

The inclusion/exclusion criteria
Inclusion criteria
Age ≥ 40 years old;
Patients with severe stenosis of the internal carotid artery;
Planned for carotid artery stent;
Modified Rankin Scale score ≤ 2;
The subject has adequate temporal bone windows to undergo TCD, and the blood flow signal of the middle cerebral artery is detectable.;
Signed informed consent by patient or their legally authorized representative.
Exclusion criteria
Comorbid conditions with severe infections or severe diseases of the liver, kidney, hematopoietic system, endocrine system, etc.;
Occurrence of intracranial hemorrhage (cerebral parenchymal hemorrhage, subarachnoid hemorrhage, subdural/epidural hemorrhage) within 90 days prior to enrollment;
Severe hematological disorders or significant coagulation abnormalities;
Pregnant or breastfeeding women;
Participation in another clinical trial within the past 3 months or ongoing participation;
Any other circumstances deemed by the investigator as unsuitable for participation in this clinical study.*

* mainly include (1) contraindications to MRI; (2) life expectancy < 1 year due to advanced malignancy or end-stage organ failure; (3) severe psychiatric or cognitive disorders precluding informed consent or follow-up compliance; (4) anticipated poor adherence to scheduled follow-up assessments. Any other rare exclusion will be recorded with detailed justification in the case report form.

### Standard protocol approvals, registrations, and patient consents

The TCD-ICAS trial was prospectively registered on ClinicalTrials.gov (NCT07462546). Ethical approval for the study protocol and procedures was granted by the Ethics Committee of the General Hospital of Northern Theater Command (IRB: Y (2026)13). Written informed consent will be secured from every participant or their legally authorized representatives before inclusion into the trial.

### Randomization and intervention

Eligible patients are randomized 1:1 into the TCD group or control group via a computer-generated sequence, stratified by collateral status (poor vs. good) and age (≤65 vs. >65 years). In TCD group, patients will receive continuous TCD monitoring using a 1.6 MHz transducer insonating the ipsilateral middle cerebral artery (M1 segment, 55 mm depth) at 100% power output (0.274 MPa). The monitoring begins at femoral artery puncture and continues until 30–60 min after CAS completion. In the Control group, patients will only receive standard perioperative care without TCD monitoring. Both groups will receive guideline-based medical management. To ensure patient safety during prolonged continuous TCD insonation, we will continuously monitor the real-time Thermal Index (TI) and Mechanical Index (MI) displayed on the ultrasound system. For the 1.6 MHz transducer used in this protocol, TI is consistently < 1.0 and MI < 1.9, both well within diagnostic safety limits. The operator will also regularly ask the patient about any local discomfort or warmth during the procedure. Any reported symptoms will be documented as adverse events and reviewed by the Data and Safety Monitoring Committee.

### Outcome measures

Primary efficacy endpoint is number of new DWI lesions at 24 (±8) hours post-randomization. Secondary efficacy endpoints include total volume of new DWI lesions; number of lesions >0.5 mL; composite of ischemic stroke, transient ischemic attack (TIA), or death within 30 (±3) days.

Safety endpoints include intracranial hemorrhage within 24 (±8) hours; serious adverse events within 24 h.

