### Follow-up procedure

All patients will undergo follow-up assessments at the following time points: before the CAS procedure, and at 24 ± 8 h, 3 ± 1 day, and 30 ± 3 days after randomization (see Table 2). Baseline evaluations will include collection of demographic information, laboratory tests, neuroimaging findings, and neurologic scores (NIHSS and mRS). Post-CAS assessments will consist of MRI (including DWI) and NIHSS at 24 ± 8 h, NIHSS at 3 ± 1 day, and mRS at 30 ± 3 days.

**Table 2 tab2:** Timing of all procedures.

Timepoint	Screening	0	24 ± 8 h	3 ± 1 days	30 ± 3 days
Eligibility screen	x				
Informed consent	x				
Randomization	x				
Head CT/MRI	x		x*		
NIHSS assessment	x	x	x	x	
mRS assessment	x				x
Medical history	x				
Population characteristics	x				
Vital signs	x	x	x	x	x
Blood routine	x				
Urinalysis	x				
Coagulation test	x				
Serum biochemistry	x				
ECG	x			x	
Concomitant medication		x	x	x	x
Adverse events		x	x	x	x
Recurrent stroke and other vascular events		x	x	x	x

CT indicates computed tomography; MRI, magnetic resonance imaging; NIHSS, National Institutes of Health Stroke Scale; mRS, modified Rankin Scale; ECG, electrocardiogram. * Diffusion-weighted imaging (DWI) is mandatory.

All clinical evaluations, including NIHSS and mRS, will be performed by qualified investigators who are blinded to TCD therapy following standardized protocol procedures. The primary efficacy outcome will also be assessed by independent neuroimaging reviewers who are blinded to treatment assignments.

Concomitant medications and adverse events occurring within 30 days after randomization will be recorded in detail by investigators and subsequently reviewed by certified adjudicators. The total duration of the study is estimated to be approximately 9 months.

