### Quality control and data management

In this clinical trial, an independent Data and Safety Monitoring Committee (DSMC) has been established to ensure continuous monitoring of data safety, e.g., with a specific focus on endpoints such as hemorrhagic events and other severe adverse events (SAEs). Rules governing study termination or sample size modification will be pre-specified by the DSMC. Once follow-up has been completed for 50% of participants, an interim analysis will be carried out by an independent statistician affiliated with the DSMC, who will not be involved in the trial’s management. Based on the outcomes of the analysis, the DSMC will be authorized to make recommendations to the Steering Committee regarding adjustments to the sample size or early termination of the study. Additionally, neuroimaging data will be collected centrally and independently assessed by two neuroradiologists.

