### Statistical analysis

Intention-to-treat analysis will be used. The primary endpoint will be analyzed using a negative-binomial generalized linear model with a log-link function. For volume of new cerebral infarcts, analysis of covariance (ANCOVA) will be used if normally distributed; log-transformation followed by ANCOVA or a non-parametric test (e.g., Mann–Whitney U test) will be applied for between-group comparison if the distribution is skewed. Number of new DWI infarcts >0.5 mL will be compared between groups using negative-binomial generalized linear model with a log-link function. For composite incidence of ischemic stroke, TIA, and death within 30 days, Kaplan–Meier curves will be plotted, and between-group event rates will be compared with the log-rank test. A Cox proportional-hazards regression model will be fitted to calculate the hazard ratio (HR) with 95% confidence interval (CI) for the TCD group versus the Control group.

All safety endpoints will be analyzed in the safety analysis set. Categorical variables (e.g., incidence of intracranial hemorrhage, serious adverse events) will be summarized as frequencies and percentages, with between-group comparisons performed using Fisher’s exact test. Continuous variables will be described as mean ± standard deviation or median (interquartile range) according to their distribution, and compared using t-tests or non-parametric tests as appropriate.

Exploratory analyses of multiple secondary endpoints will be conducted without adjustment for multiple comparisons; results are considered hypothesis-generating and should be interpreted with caution.

All statistical tests will be two-sided, with a significance level of *α* = 0.05; a *p*-value <0.05 will be considered statistically significant.

The primary outcome will further be analyzed according to subgroups: age (<60 years vs. ≥ 60 years), sex (female vs. male), history of diabetes (yes vs. no), history of hypertension (yes vs. no), degree of index vessel stenosis (70–84% vs. 85–99%), collateral status (poor vs. good). Differences in the primary outcome across the aforementioned subgroups will be evaluated by assessing the interaction effect between the pre-specified baseline variables and the primary outcome.

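### Non-fatal intracranial hemorrhage after about 32 h, and other non-fatal, non-ischemic SAEs after 24 h, are recorded to day 30 but belong to no named endpoint or stated between-arm comparison

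*Protocol article*

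**What the plan says.** All references are to the protocol article.

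- **Safety endpoints.** Outcome measures: "Safety endpoints include intracranial hemorrhage within 24 (±8) hours; serious adverse events within 24 h". The abstract agrees: "The primary safety endpoint is intracranial hemorrhage within 24 h".
- **30-day clinical endpoint.** The last secondary efficacy endpoint is the "composite of ischemic stroke, transient ischemic attack (TIA), or death within 30 (±3) days". Statistical analysis keeps the same components: "For composite incidence of ischemic stroke, TIA, and death within 30 days, Kaplan–Meier curves will be plotted", followed by a log-rank test and a Cox model.
- **Recording.** Follow-up procedure: "Concomitant medications and adverse events occurring within 30 days after randomization will be recorded in detail by investigators and subsequently reviewed by certified adjudicators". Table 2 collects adverse events, and separately recurrent stroke and vascular events, at every visit up to 30 ± 3 days.
- **Scheduled examinations.** "Post-CAS assessments will consist of MRI (including DWI) and NIHSS at 24 ± 8 h, NIHSS at 3 ± 1 day, and mRS at 30 ± 3 days". The 24 h imaging is the only imaging scheduled after the procedure.
- **Safety analysis.** Statistical analysis compares the safety endpoints by arm with Fisher's exact test in the safety set. It gives intracranial hemorrhage and SAEs as examples and adds no later window.
- **Monitoring.** Under Quality control and data management, the DSMC is to attend especially to hemorrhage and SAEs. No time limit is given.

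**The concern.** The Abstract and Introduction describe TCD as a means of enhancing fibrinolysis and the penetration of fibrinolytic drugs. Bleeding is the natural counter-risk, and intracranial hemorrhage is accordingly the primary safety endpoint. Yet the plan follows ischemic events to day 30 in a formal comparison and follows non-fatal hemorrhage for little more than a day. A patient with a non-fatal hemorrhage on day 3 remains event-free in the 30-day Kaplan–Meier and Cox analyses, unless an ischemic stroke, TIA or death follows, and is also outside both safety endpoints.

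This affects the balance of the final report. The Discussion expects TCD to improve the safety profile of stenting and to lower peri-procedural stroke in general. The named endpoints could show a 30-day ischemic benefit but give no matching 30-day comparison of hemorrhagic harm.

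**Working it through.** The article gives no figure of its own on this point. The check sets the definitions side by side and then sizes the gap.

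**1. Which endpoint counts which event**

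Inputs: the windows and components in Outcome measures, taken at their widest. For hemorrhage the limit is 24 + 8 = 32 h.

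| Event | Hemorrhage, 24 (±8) h | SAE, 24 h | 30-day composite |
|---|---|---|---|
| Non-fatal intracranial hemorrhage, up to 24 h | yes | yes, if serious | no |
| Non-fatal intracranial hemorrhage, 24–32 h | yes | no | no |
| **Non-fatal intracranial hemorrhage, 32 h to day 30** | **no** | **no** | **no** |
| **Other non-fatal, non-ischemic SAE, 24 h to day 30** | **no** | **no** | **no** |
| Non-fatal ischemic stroke or TIA, 24 h to day 30 | no | no | yes |
| Fatal event of any cause, 24 h to day 30 | only if a hemorrhage up to 32 h | no | yes, through death |

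The two rows in bold are the gap. The day-30 mRS does not close it, because it is collected but not listed as an endpoint.

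**2. Calendar time covered**

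The recording period is 30 × 24 = 720 h.

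- SAE window: 24/720 = 3.3%, leaving 96.7% outside.
- Widest hemorrhage window: 32/720 = 4.4%, leaving 95.6% outside.

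These are shares of time. The article does not say how hemorrhage risk is spread over the 30 days, so they cannot be read as shares of events.

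**3. Possible number of events**

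The Sample size calculation gives 110 per group, and 110/0.95 = 115.8, rounded up to 116. The article gives no late-hemorrhage rate. For an assumed 0.5% to 2%:

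- 116 × 0.005 = 0.58, about 0.6 per arm
- 116 × 0.02 = 2.32, about 2.3 per arm

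**4. What a comparison could show**

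Two-sided Fisher's exact test, 116 per arm:

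- 5 vs 0: p = 0.060
- 6 vs 0: p = 0.029

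With none in one arm, six patients are needed in the other for p < 0.05. At the assumed rates a test would rarely reach that. The value of a 30-day endpoint lies in a complete count and estimate by arm.

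**The case against.** **The plan does not contradict itself.** Recording adverse events for longer than the named safety window is not an inconsistency. The short window has a rationale in the text: insonation stops 30–60 min after stenting, and the one scheduled post-procedure scan is at 24 ± 8 h. This stands. The point concerns the choice of endpoints, not conflicting passages.

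**Ascertainment changes after the scan.** Hemorrhage at 24 h is sought by systematic imaging. Later hemorrhage is found only if symptoms prompt a scan. One pooled 30-day count would mix the two. This stands and shapes the fix.

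**Routine tabulation may cover it.** The list of safety endpoints is introduced with a non-exhaustive verb, the article is condensed, and a by-arm table of all adverse events is usual in a SAP. This stands in part. A reader might infer that late hemorrhages would go unreported; no passage says so, and they are recorded, adjudicated and open to the DSMC. But the windows and components are stated definitions, not omitted detail, and no later safety endpoint is named anywhere in the article.

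**An ischemic composite fits the embolism hypothesis.** Hemorrhage is kept as safety, and the composite is secondary and hypothesis-generating. This stands. A reader might infer that the composite is wrong and should be replaced; the documents do not support that, and an added analysis is enough.

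Two further readings are tempting but fail:

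- *No non-fatal SAE after day 1 is compared between arms.* Late ischemic strokes, which would ordinarily be SAEs, and TIAs that are serious are compared in the composite.
- *The safety clock starts at randomization, so part of the window can precede stenting.* Outcome measures ties only the primary efficacy endpoint to randomization. Follow-up procedure times the visits from randomization, but for the safety endpoints the start is an inference.

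**Conclusion.** The concern holds in a limited form. A non-fatal intracranial hemorrhage after about 32 h, or another non-fatal SAE after 24 h that is neither an ischemic stroke nor a TIA, is collected and adjudicated to day 30 but has no named endpoint and no stated comparison by arm.

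The definitional part rests on the text alone, with the ±8 h read at its upper limit. The likely number of patients is unknown: 0.6–2.3 per arm depends wholly on the assumed 0.5–2%, which has no basis in the documents. A reader might infer from the calendar shares that some 97% of the safety risk is missed. That figure fits only the SAE window and describes time, not risk.

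The primary efficacy analysis and the sample size are unaffected. For an intervention meant to enhance fibrinolysis, this is a worthwhile, low-cost improvement in how harm is reported.

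**What to change.** Keep the 24 h safety endpoints and the ischemic composite as they are, and add:

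1. Any intracranial hemorrhage through 30 (±3) days and any SAE through 30 (±3) days as further safety endpoints, compared by arm with the Fisher test already planned.
2. A supportive 30-day analysis of any stroke (ischemic or hemorrhagic), TIA or death, with the same log-rank and Cox methods.
3. Separate reporting of hemorrhage found on the scheduled 24 h imaging and hemorrhage detected clinically afterwards.

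State the starting point of each safety window in the same edit.

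**Cost.** No new data collection is needed. The trial is registered, ethics-approved and recruiting, with 12 patients enrolled at initial submission, so the change needs a protocol amendment and a registry update, made without reference to results by arm. Some events unrelated to TCD will enter the comparison. Counts will be low, so the added safety results should be presented mainly as descriptive.

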### Follow-up procedure

All patients will undergo follow-up assessments at the following time points: before the CAS procedure, and at 24 ± 8 h, 3 ± 1 day, and 30 ± 3 days after randomization (see Table 2). Baseline evaluations will include collection of demographic information, laboratory tests, neuroimaging findings, and neurologic scores (NIHSS and mRS). Post-CAS assessments will consist of MRI (including DWI) and NIHSS at 24 ± 8 h, NIHSS at 3 ± 1 day, and mRS at 30 ± 3 days.

**Table 2 tab2:** Timing of all procedures.

Timepoint	Screening	0	24 ± 8 h	3 ± 1 days	30 ± 3 days
Eligibility screen	x				
Informed consent	x				
Randomization	x				
Head CT/MRI	x		x*		
NIHSS assessment	x	x	x	x	
mRS assessment	x				x
Medical history	x				
Population characteristics	x				
Vital signs	x	x	x	x	x
Blood routine	x				
Urinalysis	x				
Coagulation test	x				
Serum biochemistry	x				
ECG	x			x	
Concomitant medication		x	x	x	x
Adverse events		x	x	x	x
Recurrent stroke and other vascular events		x	x	x	x

CT indicates computed tomography; MRI, magnetic resonance imaging; NIHSS, National Institutes of Health Stroke Scale; mRS, modified Rankin Scale; ECG, electrocardiogram. * Diffusion-weighted imaging (DWI) is mandatory.

All clinical evaluations, including NIHSS and mRS, will be performed by qualified investigators who are blinded to TCD therapy following standardized protocol procedures. The primary efficacy outcome will also be assessed by independent neuroimaging reviewers who are blinded to treatment assignments.

Concomitant medications and adverse events occurring within 30 days after randomization will be recorded in detail by investigators and subsequently reviewed by certified adjudicators. The total duration of the study is estimated to be approximately 9 months.

### Quality control and data management

In this clinical trial, an independent Data and Safety Monitoring Committee (DSMC) has been established to ensure continuous monitoring of data safety, e.g., with a specific focus on endpoints such as hemorrhagic events and other severe adverse events (SAEs). Rules governing study termination or sample size modification will be pre-specified by the DSMC. Once follow-up has been completed for 50% of participants, an interim analysis will be carried out by an independent statistician affiliated with the DSMC, who will not be involved in the trial’s management. Based on the outcomes of the analysis, the DSMC will be authorized to make recommendations to the Steering Committee regarding adjustments to the sample size or early termination of the study. Additionally, neuroimaging data will be collected centrally and independently assessed by two neuroradiologists.

